**Methods:**

People with a diagnosis of pharmacoresistant epilepsy will be recruited in London, United Kingdom, and Freiburg, Germany. Participants will be asked to wear a wrist-worn device and download ad hoc apps developed on their smartphones. The apps will be used to collect data related to sleep, physical activity, stress, mood, social interaction, speech patterns, and cognitive function, both passively from existing smartphone sensors (passive remote measurement technology [pRMT]) and actively via questionnaires, tasks, and assessments (active remote measurement technology [aRMT]). Data will be collected continuously for 6 months and streamed to the Remote Assessment of Disease and Relapse-base (RADAR-base) server.

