**Active** **RMT**														
	Seizure diary and precipitants	—	—	—	—	—	—	Daily questionnaire	—	—	—	—	—	—
	ESM^f^ assessment	✓	—	—	✓	—	—	✓	—	—	✓	—	—	✓
	Cognition	✓	—	—	✓	—	—	✓	—	—	✓	—	—	✓
	Speech task	✓	✓	✓	✓	✓	✓	✓	✓	✓	✓	✓	✓	✓
	Mood PHQ8^g^ (A^h^)	✓	✓	✓	✓	✓	✓	✓	✓	✓	✓	✓	✓	✓
	Anxiety GAD7^i^ (A or W^j^)	✓	—	—	—	—	—	✓	—	—	—	—	—	✓
	Self-esteem RSES^k^ (A)	✓	—	—	—	—	—	✓	—	—	—	—	—	✓
	Quality-of-life WSAS^l^ (A or W)	✓	—	—	—	—	—	✓	—	—	—	—	—	✓
	BIPQ^m^ (A or W)	✓	—	—	—	—	—	✓	—	—	—	—	—	✓
	Change in medications (T^n^ or F2F^o^)	—	—	✓	—	—	—	✓	—	—	—	—	—	✓
	CSR^p^ (T or F2F)	—	—	✓	—	—	—	✓	—	—	—	—	—	✓
	LTE-Q^q^ (T or F2F)	—	—	✓	—	—	—	✓	—	—	—	—	—	✓

^a^—: Task or assessment not required.

^b^✓: Task or assessment required.

^c^TAM-FF: Technology Assessment Model Fast Form.

^d^PSSUQ: Post-Study System Usability Questionnaire.

^e^RMT: remote measurement technology.

^f^ESM: experience sampling method.

^g^PHQ8: 8-item Patient Health Questionnaire.

^h^A: assessed via app.

^i^GAD7: 7-item Generalized Anxiety Disorder questionnaire.

^j^W: web-based assessment.

^k^RSES: Rosenberg Self-esteem Scale.

^l^WSAS: Work and Social Adjustment Scale.

^m^BIPQ: Brief Illness Perceptions Questionnaire.

^n^T: telephone assessment.

^o^F2F: face to face assessment.

^p^CSRI: Client Service Receipt Inventory.

^q^LTE-Q: List of Threatening Experiences Questionnaire.

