### Study Procedures

Participants will be recruited over 6 months from the Epilepsy Service and Clinical Neurophysiology Department at King’s College Hospital, London, and from the Epilepsy Center, Department of Neurosurgery, University of Freiburg, Germany.

Potentially eligible individuals will be identified among those attending a routine outpatient appointment or hospital video–EEG EMU admission or home video–EEG monitoring appointment at the participating sites. These individuals will be approached by a member of the on-site research team and given the study information sheet and consent form.

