### Contextual Variables

Variation in self-esteem will be measured using the Rosenberg Self-Esteem Scale [48], a 10-item self-reported questionnaire. QoL or disability will be measured using the Work and Social Adjustment Scale [49], a 5-item assessment of perceived social and work-related functional impairment used widely across a range of mental and physical disorders. Illness perceptions will be assessed using the Brief Illness Perceptions Questionnaire [50], which provides an insight into participants’ views about their underlying conditions, including a measure of how well they see themselves coping with its symptoms and treatments.

We will seek to identify major changes in participants’ circumstances that may materially affect participants’ outcomes and may also impact the use of RMT. In particular, we will collect information about change in medications for epilepsy, health service utilization (the modified Client Service Receipt Inventory [CSRI]) [51], and change in life circumstances (List of Threatening Experiences Questionnaire [LTE-Q]) [52].

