We will develop an analysis strategy for managing multi-sensor data. To this end, we will investigate what type of features derived from the pRMT and aRMT correlate with seizure occurrence and frequency per unit of time (eg, day and week). Seizure occurrence and frequency will be derived from the multiparametric wearable system and from seizure diaries and analyzed separately. Data obtained from wearable biosensors will be used to derive information about participants’ activity during the day and information about sleep and mood. Aggregated features obtained from biosensors, smartphones, and cognitive tests and from ESM and their changes from baseline or previous time points (delta features) will be used for statistical analysis. First, we will use a univariate approach, where the number of seizures per unit of time will be modeled with each variable or feature as a fixed effect and participant as a random effect. Demographics and other baseline characteristics will be added to the model when necessary. Correction for multiple comparisons will be taken into account. Second, using aggregated data obtained through some time duration to predict the number of seizures per the same time duration, we will construct predictive models. Under the assumption that data are missing at random, multiple imputation will be applied for covariates, where missingness is not drastically high. Multivariate prediction models will be constructed, and variable selection, based on, for example, least absolute shrinkage and selection operator L1-regularization for linear models, or different feature selection algorithms will be applied. Model performance will be characterized through cross-validation, putting stress on the sensitivity and specificity of the predictive model.

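### The univariate seizure-frequency models name only baseline adjustment, so a medication change during follow-up can make an RMT feature appear to influence seizure frequency

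*Protocol article*

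**What the plan says.** All references are to the protocol article.

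- **Seizure model (Statistical Analysis Plan).** In the first step, the number of seizures per unit of time is "modeled with each variable or feature as a fixed effect and participant as a random effect". Adjustment is described in one sentence: "Demographics and other baseline characteristics will be added to the model when necessary". The feature sources named are "Aggregated features obtained from biosensors, smartphones, and cognitive tests and from ESM", including changes from baseline or from earlier time points.
- **Usability model (same section).** The mixed model for PSSUQ and TAM-FF takes duration in the study and contextual variables as covariates. CSRI and LTE-Q are given as examples.
- **Medication change (Contextual Variables).** The article says that "we will collect information about change in medications for epilepsy", alongside CSRI and LTE-Q. The reason given is that such changes in circumstances are ones "that may materially affect participants’ outcomes and may also impact the use of RMT". Table 1 schedules the record at weeks 4, 12 and 24.
- **Aim (Study Outcomes).** The second secondary outcome is to identify which variables influence the long-term course of seizure frequency.
- **Population.** The abstract says: "People with a diagnosis of pharmacoresistant epilepsy will be recruited in London, United Kingdom, and Freiburg, Germany". The inclusion criteria ask for a diagnosis of epilepsy and an average of at least 2 seizures per month. They contain no criterion for drug resistance or stable medication.

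**The concern.** The article does choose an adjustment set for the seizure counts, and every item in it is fixed at baseline. Contextual variables and time in study are named for the usability scales but not for seizure frequency, the outcome on which epilepsy medication acts most directly.

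A random intercept and baseline covariates account for differences between people. They cannot account for something that changes within a person during follow-up. If a new regimen lowers seizure frequency and also alters sleep, activity, mood or cognition, the feature and the seizure count move together without either acting on the other. Change-from-baseline features would carry the same shift. The feature could then be reported as a variable that influences seizure frequency, which is what the secondary outcome sets out to find. Correction for multiple comparisons lowers the threshold for a finding but does not remove this bias.

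**Working it through.** The article gives no rate of medication change, no effect of it and no feature shift, so there is no planned figure to reproduce. The check has three parts.

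**1. Where medication change appears**

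| Place | Medication change or contextual variables |
|---|---|
| Contextual Variables | Collected; may affect outcomes and RMT use |
| Usability model | Contextual variables named as covariates (medication change by implication) |
| Univariate seizure model | Not named; baseline characteristics only |
| Multivariate seizure model | Not named; could enter as an aRMT variable |

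**2. Size of the bias by hand**

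Take a feature with no effect on seizures and within-person SD 1. Let a share *q* of participants change regimen, with rate ratio *RR* for seizures and a feature shift of *d* SD afterwards. To a linear approximation the spurious log rate ratio per SD is

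*b* ≈ *d* · ln(*RR*) · *V* / (1 + *d*² · *V*), with *V* = *q* · mean of *p*(1 − *p*),

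where *p* is the fraction of follow-up after the change. With 24 weeks and 5 to 20 of them after the change, equally likely, the mean of *p*(1 − *p*) is (24 × 12.5 − 177.5)/576 = 0.213. For *q* = 0.5, *V* = 0.106.

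- *d* = 1, *RR* = 0.5: *b* ≈ −0.693 × 0.106/1.106 = −0.067, a rate ratio of 0.94 per SD.
- *d* = 0.5, *RR* = 0.5: *b* ≈ −0.5 × 0.693 × 0.106/1.027 = −0.036, a rate ratio of 0.96.
- *d* = 0 or *RR* = 1: *b* = 0.

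The bias is essentially a product, so it disappears if any one factor is absent.

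**3. Simulated false-positive rate**

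From the article: 32 participants, 24 weeks, at least 2 seizures per month. Assumed: *q*, *RR*, *d*, Poisson weekly counts, and changes unrelated to the earlier seizure course. The analysis was a participant-stratified Poisson model, two-sided 0.05, with 600 replicates. Monte Carlo error around 5% is about 2 × √(0.05 × 0.95/600) = 1.8 points. Selected rows:

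| Share changing | RR | Shift (SD) | No medication term | With term | Mean spurious RR, no term |
|---|---|---|---|---|---|
| 10% | 0.5 | 1 | 6.3% | 5.8% | 0.988 |
| 25% | 0.5 | 0.5 | 6.5% | 4.5% | 0.981 |
| 25% | 0.5 | 1 | 6.7% | 3.5% | 0.973 |
| 50% | 0.8 | 1 | 7.0% | 5.8% | 0.982 |
| 50% | 0.5 | 0 | 4.7% | 4.3% | 1.000 |
| 50% | 0.5 | 0.5 | 10.7% | 6.7% | 0.968 |
| 50% | 0.5 | 1 | 23.3% | 6.0% | 0.941 |

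The simulated rate ratios agree with the hand formula. Over the full grid the rate with the term was 3.5–6.7%.

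Two further sets of runs used the same frame with other details:

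- **Half changing mid-study, 400 replicates.** Without and with the term: 32% and 5% (RR 0.5, 1 SD), 14% and 4% (RR 0.5, 0.5 SD), 10% and 5% (RR 0.6, 0.5 SD). Change at mid-study maximises *p*(1 − *p*) at 0.25, one reason for higher values than in the table.
- **1,500 replicates, no term.** 35% (half changing, RR 0.5, 1 SD), 12.5% (a quarter changing, same effects), 5.9% (a quarter, RR 0.7, 0.5 SD), 5.8% (half, RR 0.8, 0.5 SD). The 35% fell to 8% when the direction of the feature shift differed between patients.

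**The case against.** The strongest reply is that the text does not exclude medication from the seizure analyses. Candidate features come from both passive and active RMT, Table 1 lists the medication-change record under Active RMT, and daily compliance and ESM medication use are also collected. The multivariate step could select any of these. This stands: a reader might infer that all seizure models ignore medication, but the documents support that only for the adjustment named at the univariate step. They do not say that the multivariate step will use the medication-change record.

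A second reply is that a condensed article may leave a covariate list to the full plan. That would answer a silent text. This one names an adjustment set, and the set does not match its own reason for collecting medication change.

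Third, for pure prediction an omitted confounder does not in itself spoil predictive performance. That is correct, and it limits the concern to the explanatory outcome.

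Fourth, the tests will be corrected for multiplicity. With Bonferroni over an assumed 20 features, the strongest case falls to 8% and a mild one (half changing, RR 0.6, 0.5 SD) to 1%. The nominal level is then 0.05/20 = 0.25%, so the relative inflation remains, but 32% or 35% is not the error rate of the planned test.

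Finally, recruitment is partly from routine care ("Potentially eligible individuals will be identified among those attending a routine outpatient appointment"). A reader might infer that regimen changes will be common, or that the missing pharmacoresistance criterion causes the confounding. The article gives no rate of change. Neither population statement requires stable medication, and nothing says that drug-resistant patients change treatment less.

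**Conclusion.** The point holds for the univariate seizure-frequency models and the explanatory secondary outcome. The only adjustment they name cannot remove a within-person treatment change that the study itself records as relevant. Such a change can therefore make a null feature look influential; the documents do not show that it will.

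Under the assumed inputs, the uncorrected false-positive rate stays near 5% when changes are few, weak or do not shift the feature. It is roughly 10–35% when half of participants change regimen, seizures halve and the feature shifts 0.5–1 SD in a consistent direction. With a quarter changing and the same strong effects at 1 SD, the runs gave 6.7% and 12.5%. A medication term restores about 5%. The change is worth making because it is cheap, but it concerns a secondary outcome and does not touch the primary one.

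The population mismatch is a separate inconsistency that needs no assumptions. The abstract and the inclusion criteria describe different groups, and reconciling them would not repair the model.

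**What to change.** 1. Record the date of each medication change at the scheduled week 4, 12 and 24 contacts. The article mentions no such date. Without it, a change first reported at week 24 could lie anywhere in the preceding 24 − 12 = 12 weeks.
2. Include a time-varying medication-change term in each univariate seizure model, and name it as a candidate or forced covariate in the multivariate models.
3. Add a sensitivity analysis restricted to periods without medication change.
4. Treat time since enrolment as optional, since it could absorb part of the long-term trajectory that the study wants to explain.
5. Separately, reconcile the population in the abstract with the inclusion criteria.

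The cost is one date field, one or two more parameters per model and a few sentences of text. The restricted sensitivity analysis will use fewer observations.

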### Study Objectives

The main aims of the RADAR Epilepsy study are (1) to determine the usability and acceptability of RMT to provide real-time objective multidimensional indications of clinical state in individuals with epilepsy; (2) to assess the correspondence of patient-marked seizure events (via aRMT) with the data collected from the pRMT; and (3) To determine whether multiparametric RMT collected in populations with epilepsy can prospectively estimate variations in seizure occurrence and other outcomes, including seizure frequency, QoL, and comorbidities.

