Seizure occurrence and precipitants: Each evening, participants will be prompted to complete a daily assessment to provide self-reported information about medication compliance, sleep quality, alcohol use, menstrual cycle, stress, mood, anxiety, and seizure occurrence. If a seizure is reported, the participant will be automatically directed to an ad hoc created seizure diary. Information on clinical symptoms and manifestations, time of the event, and possible precipitants will be collected through the diary.Experience sampling method: Participants will be asked to complete a series of short electronic diary assessments, also known as the experience sampling method (ESM). ESM assesses experiences and behavior in the realm of daily life and will be administered to provide real-time self-reported data on mood, stress, cognition, activity, location, social interactions, physical state, and medication use. An ESM period will be initiated once every 6 weeks, during which participants will receive notifications to complete 9 questionnaires per day over a 6-day period (semirandom interval between 8:30 AM and 10 PM).
Speech task: On a random schedule, participants will be asked to hold down a button on their phone to start recording and will then be asked to say aloud, and in a quiet area, some excerpts from *The North Wind and the Sun*, which are shown to be phonetically balanced in different languages. In addition, participants will be asked to respond to the following question: *Can you describe something you are looking forward to this week?* These data will be recorded in a raw audio format, allowing speech recognition to extract content and automatic sentiment detection.Cognitive function: Cognitive assessment will use the THINC-ITapp, which has been validated to screen for cognitive dysfunction [45] and examines executive functions, such as memory, attention, and concentration.

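### The seizure prediction models do not require features to precede the seizures they predict, so as written they estimate concurrent association and do not test the aim of prospective estimation

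*Protocol article*

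**What the plan says.** Study Objectives lists three main aims. The third is to determine whether multiparametric remote measurement "can prospectively estimate variations in seizure occurrence and other outcomes, including seizure frequency, QoL, and comorbidities".

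The Statistical Analysis Plan serves that aim in two steps. In the univariate step, "the number of seizures per unit of time will be modeled with each variable or feature as a fixed effect and participant as a random" term. In the second step, the predictive models are built by "using aggregated data obtained through some time duration to predict the number of seizures per the same time duration". Neither step states a lag or a lead time. The only backward-looking element is that aggregated features and "their changes from baseline or previous time points (delta features) will be used for statistical analysis". On the outcome side, "Seizure occurrence and frequency will be derived from the multiparametric wearable system and from seizure diaries and analyzed separately".

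Study Technology describes one assessment each evening that asks about sleep quality, stress, mood and anxiety together with whether a seizure occurred. A reported seizure opens a separate diary: "Information on clinical symptoms and manifestations, time of the event, and possible precipitants will be collected through the diary".

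**The concern.** A prospective claim needs the predictor to be measured before the outcome. Here the order is either absent (one shared window) or unstated (two windows of equal length).

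The way the data are collected makes this matter:

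- A day's stress, mood and anxiety ratings are given in the evening, after any daytime seizure, in the same sitting as the seizure report.
- Sleep and activity can change after a seizure.
- The wristband records movement, pulse-derived measures and electrodermal activity. The Background names these as channels in which seizures show themselves, so the ictal signal can enter the feature.
- The wearable also supplies one of the two versions of the seizure count, so feature and outcome may come from the same signal.

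At stake is the interpretation. A model that recognises days on which a seizure has already happened could be presented as one that anticipates seizures. The abstract's Conclusions and the Discussion both speak of identifying preictal states.

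**Working it through.** The plan states no effect size, power or error rate for the prediction models, so there is no figure to reproduce. The check reads the text for time order, then sizes the problem.

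**1. Time order in the text.** The predictive step uses one duration for features and seizures. The univariate step uses one unit of time for both. A change from a previous time point is the current value minus an earlier one, so a delta feature still contains the current window and creates no lead. No other section of the article sets an order.

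**2. Planned safeguards.** Cross-validation scores held-out windows that carry the same ictal and post-ictal information. Multiplicity correction does not remove an association that is real but runs from seizure to feature. L1 selection would tend to keep such a feature.

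**3. Inputs for the illustration.**
- From the protocol article: 32 participants; 24 weeks (168 days) in Table 1; at least 2 seizures per month from the inclusion criteria; day or week as the unit.
- Assumed: Poisson seizures; a feature that moves by b SD in the same window as a seizure and has no effect on later seizures; b = 0.3, 0.5 or 1.0. The documents give no value for b.

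Expected seizures at the minimum rate: 32 × (168 / 30.4375) × 2 = 353.

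**4. Same-day analysis, closed form.** For a normal feature shifted by b SD, AUC = Φ(b/√2). The test statistic is roughly b × √353 = 18.8b.

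| b (SD) | AUC = Φ(b/√2) | approximate z | simulated AUC | runs significant |
|---|---|---|---|---|
| 0.3 | 0.584 | 5.6 | 0.588 | 100% |
| 0.5 | 0.638 | 9.4 | 0.642 | 100% |
| 1.0 | 0.760 | 18.8 | 0.765 | 100% |

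The simulation used 500 runs per setting, a within-participant slope and a cluster-robust standard error. At 4 seizures per month the AUC is 0.589 to 0.770. With b = 0 it is 0.50, with about 6% of runs significant.

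**5. One-day lag.** The same reactive feature on day t, set against seizures on day t+1, gives AUC 0.498 to 0.500 and is significant in about 3% to 7% of runs.

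**6. Weekly analysis at b = 0.5.** The answer depends on how a one-day reaction carries into the weekly feature.
- If the weekly feature itself moves by 0.5 SD per seizure, 100% of runs are significant (AUC 0.66).
- If seven independent days are averaged, the shift is diluted to 0.5/√7 = 0.19 SD. Then z is about 0.19 × 18.8 = 3.6, which implies rejection in about 94% of runs. Simulations gave 85% and 92%.
- With day-to-day autocorrelation of 0.3, 0.5 and 0.7 in the averaged feature, simulated rejection falls to 78%, 57% and 41%.

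With a one-week lag, AUC is 0.487 to 0.501 across all settings. Rejections run from 4% to 14%. The excess over 5% is in the wrong direction (AUC below 0.5) and comes from within-person centring of a short series; it is not predictive signal.

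**The case against.** **Equal length, not identical window.** In the same paragraph the plan speaks of features that "correlate with seizure occurrence and frequency per unit of time (eg, day and week"), where the unit of time is a rate denominator. On that reading the sentence only pairs daily features with daily counts and weekly with weekly. This is a fair reading, so it cannot be asserted that the windows are certainly identical. It does not rescue the plan, because the order of the two windows then remains unset.

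**The univariate step is openly correlational.** This stands. A concurrent model is no error there, provided its results are reported as association.

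**Diary precipitants.** A reader might infer that precipitant items recorded only after a seizure will be used as predictors, with no counterpart on seizure-free days. The documents do not say so. Sleep, alcohol, medication compliance, stress and mood are asked every evening whether or not a seizure occurred, and those items can satisfy the listing of seizure precipitants under Study Outcomes.

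**The authors know the timing problem.** The Discussion criticises arbitrary windows in earlier work, including day-before data set against next-day seizures. It suggests that horizons may differ by factor. The data would allow ordering: the diary records when a seizure happened, the sensors run continuously, and experience sampling is repeated within the day. That argues against imposing one fixed lag. It does not supply a time order.

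**Detail left to a fuller plan.** Exact lags and post-ictal exclusions may reasonably sit there. But the article states a rule, and that rule does not match the stated aim.

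**Size.** The shift b is assumed, and an AUC near 0.64 is not high accuracy. Both points stand.

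**Conclusion.** The concern holds. Followed literally, the stated prediction model estimates concurrent association. Read generously, it leaves the time order open. Either way it does not test prospective estimation.

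The size rests on an assumed same-day reaction of 0.3 to 1.0 SD and no true prospective effect. Under those assumptions, same-day AUC is about 0.58 to 0.77 with near-certain significance, against about 0.50 with a one-period lag. The weekly false-positive rate is inflated but has no single value: about 41% to 100% at 0.5 SD.

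It would go too far to conclude that every feature will be a false predictor. The problem applies to features that respond to seizures. Nor does it reach the primary outcome of acceptability and usability. It bears on a secondary outcome that serves one of the three main aims.

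**What to change.** In the Statistical Analysis Plan, replace the sentence on predictive models with wording to this effect:

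- Features from window t, including delta features, predict seizures in window t+1. The feature window ends before the outcome window begins.
- Lead times are prespecified and may be shorter or longer for different features, in line with the Discussion.
- Ictal and post-ictal data are removed from the feature window, or preceding seizures enter as a covariate.
- For daily questionnaire items, the previous evening's report is used.
- If diary precipitant items triggered by a reported seizure are considered at all, they are not used as predictors.
- Same-window and univariate results are reported as concurrent association only.

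The cost is wording, with no new data collection. Lagged effects will be smaller, and one window per participant is lost: 1 of 168 days or 1 of 24 weeks with a one-period lag.

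### The predictive models target a seizure count, but the stressed performance measures need a yes/no event that is not defined for this step

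*Protocol article*

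**What the plan says.** All of the relevant text is in the protocol article, section Statistical Analysis Plan, in the paragraph on multi-sensor data. It describes three steps.

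- **Correlation step.** The investigators will look for features that "correlate with seizure occurrence and frequency per unit of time (eg, day and week").
- **Univariate step.** Features are entered singly as fixed effects in a model for the seizure count, with a random participant term. Baseline characteristics may be added if needed.
- **Predictive step.** The target is given as follows: "using aggregated data obtained through some time duration to predict the number of seizures per the same time duration, we will construct predictive models". Variable selection is to rest on, as an example, "least absolute shrinkage and selection operator L1-regularization for linear models, or different feature selection algorithms will be applied". The yardstick, to be assessed in cross-validation folds, is then stated as "putting stress on the sensitivity and specificity of the predictive model".

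For the predictive step the section gives no event, cut-off, count-error measure or calibration measure. It also gives no fold unit and no benchmark.

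The models serve the third aim under Study Objectives, which concerns prospective estimation of variation in seizure occurrence and other outcomes. They also serve the second of the secondary outcomes under Study Outcomes. The primary outcome is acceptability and usability.

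**The concern.** The section fixes both the quantity to be predicted and the measure by which prediction will be judged, and the two are of different kinds. A predicted number of seizures has an error, a deviance and a calibration. It has no sensitivity or specificity until somebody decides which counts are positive and which predicted values call them positive. If those decisions are made after results are seen, the reported performance depends on them.

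The second matter is what such figures would mean. The third aim is about change over time, and the Discussion (Principal Findings) stresses fluctuation from day to day and within a day. Eligibility sets a minimum of 2 seizures per month and no maximum, so usual rates may differ widely among the 32 participants. A measure taken across participants can then give credit for separating people with many seizures from people with few. That could be read as seizure prediction when the model cannot tell a person's bad days from their good ones.

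**Working it through.** The article states no performance figure or sample-size calculation for the predictive models, so there is none to reproduce. The check has two parts.

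**1. Target against yardstick (text only, no assumptions)**

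- Target: "to predict the number of seizures per the same time duration, we will construct predictive models". This is a count per window.
- Yardstick: "putting stress on the sensitivity and specificity of the predictive model". This needs a binary truth and a binary prediction.
- Could another sentence supply the event? Seizure occurrence is named in the correlation step, not as the target of the predictive models. The sensitivity and false alarm rate in the preceding paragraph compare wearable detections with the diary, which is a different question. Neither defines an event here.

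The missing definition matters because the natural event, at least one seizure in the window, changes greatly with the window. Take the eligibility minimum of 2 per month, assume Poisson counts and use 30.44 days per month. The daily rate is 2/30.44 = 0.0657.

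| Window | P(no seizure) | P(at least one) |
|---|---|---|
| Day | exp(-0.0657) = 0.936 | 0.064 |
| Week | exp(-7 x 0.0657) = 0.631 | 0.369 |
| Month | exp(-2) = 0.135 | 0.865 |

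The predictive step names no window length; day and week appear only as examples in the correlation step.

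**2. What the measures show when only the person's rate is known (simulation)**

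*Inputs from the article:* 32 participants; 24 weeks (168 days) from the schedule of events; minimum 2 seizures per month.

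*Assumptions, not in the article:* Poisson counts at a constant rate per person, so there is nothing within a person to predict; lognormal rates with median 4 per 30 days, floored at 2; SD of log rate varied; event = at least one seizure in the window; results calculated across all participants.

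*Predictor:* the participant's own mean rate from the training records, under 10-fold cross-validation that splits records, not people. The cut-off maximises sensitivity + specificity - 1 on the scored data, so those two columns are slightly favourable. The null row shows by how much: 0.508 + 0.522 = 1.03 for daily windows, where chance gives 1.

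| SD of log rate | Daily AUC | Daily sens / spec | Weekly AUC | Weekly sens / spec |
|---|---|---|---|---|
| 0 | 0.50 | 0.51 / 0.52 | 0.49 | 0.50 / 0.55 |
| 0.5 | 0.62 | 0.58 / 0.62 | 0.66 | 0.58 / 0.70 |
| 1.0 | 0.73 | 0.65 / 0.71 | 0.75 | 0.62 / 0.80 |

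Two variations test whether this depends on splitting records at random.

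- Mean rate from the first half of follow-up, tested on the second half: daily AUC 0.50, 0.62, 0.69 and 0.73 at SD 0, 0.5, 0.8 and 1.0; weekly AUC 0.66, 0.72 and 0.75 at SD 0.5, 0.8 and 1.0.
- A simulated 3-month pre-study seizure frequency as the only predictor: AUC 0.73 daily and 0.75 weekly at SD 1.0. Splitting folds by participant therefore does not remove the effect if baseline frequency is a predictor.

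Because each person's rate is constant by construction, all of the apparent performance comes from differences between people.

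**The case against.** The strongest reply is that this is a condensed article. Cut-offs, fold units, link functions, offsets and calibration are ordinary analysis-plan detail, and an event may be defined in a document that is not shown. Seizure occurrence and seizure frequency are also named as separate quantities elsewhere, so a binary outcome may be what the authors had in mind. This reply stands for the omitted detail, which is not a finding. It does not remove the mismatch: the article itself states a count target and a classification yardstick in the same step.

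Three stronger readings are tempting and are not supported.

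- **That the plan commits to linear regression on counts**, with negative predictions and the wrong variance. "least absolute shrinkage and selection operator L1-regularization for linear models" is introduced only as an example of variable selection, and other algorithms are allowed. A penalised count model would fit the current wording.
- **That the reported measures will be inflated.** The article does not say that results are pooled over participants or that folds split records. The listed features are aggregates from sensors, smartphones, cognitive tests and experience sampling, with changes from earlier values, which are directed at change over time. A person's mean seizure rate is not among them, and baseline characteristics are mentioned for the univariate step. With folds split by participant and no past rate among the predictors, the effect would be weaker.
- **That sparse days make the measures look good by themselves.** A rule that never predicts a seizure has sensitivity 0, so stressing both measures exposes it at once.

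**Conclusion.** The mismatch holds on the text alone: the predictive step targets a count, stresses sensitivity and specificity, and defines no event to connect them.

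The between-person effect is a risk, not a demonstrated bias. It needs measures calculated across participants, a model that can reach the person's usual rate, and real spread in rates. The article gives no such spread. Over the assumed range, SD of log rate 0 to 1.0 with median 4 per month and floor 2, mean rate alone gives a daily AUC from 0.50 to about 0.73. AUC is used here as a summary free of any cut-off; the article does not name it. The corresponding sensitivity and specificity at SD 1.0 are about 0.65 and 0.71.

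The point is a cheap improvement on a secondary aim. The acceptability and usability conclusions are unaffected.

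**What to change.** Choose one of two routes for the predictive step and state it.

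1. **Binary.** Define the event as a seizure-day or seizure-week (yes/no), set the cut-off within the training folds, and keep sensitivity and specificity.
2. **Count.** Keep the number of seizures as the target, name a count model as the example in place of a linear one, and report out-of-sample deviance and calibration.

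On either route, report performance within participants, beside a benchmark that holds only the participant's own prior mean rate. Improvement over that benchmark is what speaks to variation over time.

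The cost is a few sentences, standard software and a little more analysis. No extra data are needed. The downside is that reported performance will probably look less favourable.
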